**5.** **STUDY OBJECTIVES**

***5.1.*** ***Primary Objective***

To explore Palonosetron absorption after subcutaneous administration, as compared with intravenous administration.

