**6.** **TYPE OF TEST REPORT AND STUDY DESIGN**

***6.1.*** ***Type of clinical trial***

Pilot clinical trial Phase I, single-center, open-label, single dose, with two periods of administration, controlled crossover study. It will randomize the sequence of administration of study medication.

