***6.2.*** ***Randomization***

Subjects will be randomly assigned to each of the two treatment sequences.

The randomization number will be the one used to identify patients included in the study and will be reflected in the documents of the study.

Randomization was performed when deciding the administration of the first dose of medication. It will randomize the order of the route of administration under consideration by the list in Annex IX.

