***8.2.*** ***Dosing Schedule***

This is a single dose study. Patients will receive on two separate occasions a single palonosetron dose of 250 μ g, once the administration is subcutaneous, intravenous in the other. The order of the route of administration will be allocated according to a randomization table.

*8.2.1.*        *Procedures medication administration*

The administration of medication will be as follows:

- First cycle: sc or iv administration, 30-60 minutes before chemotherapy administration.

- Second cycle: sc or iv infusion (the opposite way than first cycle), 30 - 60 minutes before the administration of chemotherapy

The order of the route of administration depends on the randomization table. The administration will be in the abdomen when subcutaneously. In the case of intravenous administration, the same route may be used in place for administration of chemotherapy or other medications that the patient should receive as their medical criteria.

Intravenous administration will be performed quickly, in 30 seconds, as described in the Product data sheet.

Subcutaneous administration will also perform at this time, in the abdomen.

*8.2.2.*        *Washout*

Has established a washout period between the two administrations of 14 days, which is considered sufficient as the pharmacokinetic data observed palonosetron in the literature.

*8.2.3.*        *Precautions, antidotes*

Available emergency equipment and standard operating procedure for the treatment of non-specific reactions (allergy, anaphylactic shock). At all times there will be a doctor reachable to respond to unforeseen developments.

*8.2.4.*        *Procedures blind*

It is an open, not hidden treatments either the researchers nor the volunteers, but for those responsible for drug quantification analysis.

*8.2.5.*        *Concomitant medication*

The investigator assessed the impact on the study in the event that any of the volunteers had to receive some treatment concomitantly.

Will try the two periods of administration of study medication are similar in concomitant medication.

*8.2.6.*        *Adherence*

Adherence will be secured by the research team, who directly administer the medication. Log the exact times of drug administration and removal of samples.

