**10.** **RESPONSE EVALUATION**

***10.1.*** ***Pharmacokinetic evaluation***

The quantification will be palonosetron concentrations in the Laboratory of Pharmacokinetics. Clinical Research Unit. University Clinic of Navarra. The Center is certified in Good Laboratory Practices.

With plasma concentration data at different times are calculated palonosetron pharmacokinetic parameters.

Primary parameters are considered in this study:

Cmax = maximum concentration. Its value will be extracted from the experimental data.

AUC _0-t_ = Area under the plasma concentration curve from time 0 to the last quantifiable concentration (time t) calculated by the trapezoidal method.

tmax =               time to reach Cmax. Its value will be extracted from the experimental data.

Security variables are:

VAS at different measurement times (baseline, and after the administration at 1, 4 and 8 hours)

Exploration of the administration at the same times.

The safety variables also include the description of the adverse events reported by patients or alterations in tests.

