**12.** **STATISTICS**

***12.1.*** ***Statistical methods***

The pharmacokinetic and statistical analysis of the data will be performed by UIC in the University Clinic of Navarra.

Pharmacokinetic analysis was performed on the data of concentrations of all evaluable volunteers completed the study as set forth in the protocol: pharmacokinetic profile with both formulations. The following pharmacokinetic parameters of palonosetron, will be determined for each subject following administration of each treatment:

-Cmax = maximum concentration,

-AUC _0-t_ = area under the curve versus time to the last quantifiable sample (time t), calculated using the trapezoidal method.

-Tmax = time of Cmax is reached,

-The elimination half-life, t _1/2_ , will be determined by the following expression:

t _½_ = ln 2 / k _e_

There will be a descriptive analysis of palonosetron pharmacokinetic parameters after subcutaneous administration.

Bioavailability is calculated in this way by calculating the ratio of AUC _0-t_ obtained after subcutaneous and intravenous administration.

Other parameters (analytical data, blood pressure) were analyzed using Student t test for paired data or ANOVA as appropriate, after having determined that the conditions for applying these tests. In the case of non compliance will be analyzed using appropriate nonparametric tests (Wilcoxon, Friedman).

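### The objective compares subcutaneous with intravenous absorption in a randomised crossover, but section 12.1 plans only a subcutaneous description and an AUC ratio with no interval

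*Protocol*

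**What the plan says.** The primary objective (Protocol, section 5.1) is: "To explore Palonosetron absorption after subcutaneous administration, as compared with intravenous administration". Section 10.1 ("Primary parameters are considered in this study") lists Cmax, AUC0-t and tmax. Section 6.1 describes a crossover with two administration periods, and section 6.2 adds: "Subjects will be randomly assigned to each of the two treatment sequences".

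Section 12.1 then assigns methods by type of parameter:

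- **Derivation.** Cmax, AUC0-t, tmax and half-life "will be determined for each subject following administration of each treatment", so iv values will exist for each patient.
- **Analysis of these parameters.** "There will be a descriptive analysis of palonosetron pharmacokinetic parameters after subcutaneous administration". Iv is not mentioned in that sentence.
- **Sc/iv comparison.** Bioavailability is the ratio of AUC0-t after the two routes. Nothing is said about scale, how individual ratios are combined, or an interval. Cmax and tmax have no sc/iv comparison.
- **Paired t test, ANOVA, Wilcoxon, Friedman.** These go to the other parameters, with laboratory data and blood pressure as the examples. Section 11.1.2 also gives the paired t test to laboratory values and vital signs.

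The 0.05 significance level in section 12.2 is tied to no pharmacokinetic comparison.

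**The concern.** The question is comparative and each patient is their own control, yet the stated analysis of the primary parameters covers one route and adds a single ratio. Methods that use the pairing are named for safety data and not for the primary parameters. Because section 12.1 makes this allocation itself, a later analysis plan written to follow it would carry it forward.

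What is at stake is how the main result can be read. Section 7.1 says 25 patients are enough to describe sc pharmacokinetics, including bioavailability. Without an interval nobody can judge that. An unqualified ratio can also be computed in several ways that give different answers. Finally, the two periods fall in different chemotherapy cycles, and section 8.2.5 offers only an intention on co-medication: "Will try the two periods of administration of study medication are similar in concomitant medication". A period difference is therefore possible, and section 12.1 does not say whether it will be separated from the route effect.

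**Working it through.** **The plan's own figure.** Section 7.1 gives 25 patients with no effect size, standard deviation, power, precision or margin. There is nothing to reproduce, and no figure in the protocol is shown to be wrong.

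**Inputs.** N = 25 (sections 7.1, 7.6), taken as sequences of 13 and 12, with 15 and 10 as a less balanced case. The table in section 4.1.2 gives between-subject CVs of 22% and 25% for AUC, and 61% and 44% for Cmax. The protocol gives no within-patient CV (CVw), so every CVw below is an assumption. A 20% period effect is also an assumption; none is documented.

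**1. Interval for the sc/iv geometric mean ratio.** The model for the log parameter has sequence, period, route and patient within sequence.

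sw² = ln(1 + CVw²); SE = sw × √[½(1/n1 + 1/n2)]; 90% limits = estimate × exp(± t × SE), with t(0.95; 23 df) = 1.714.

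At 13/12, √[½(1/13 + 1/12)] = 0.283.

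| Assumed CVw | sw | 90% limits as multiples of the estimate |
|---|---|---|
| 20% | 0.198 | 0.91 to 1.10 |
| 25% | 0.246 | 0.89 to 1.13 |
| 30% | 0.294 | 0.87 to 1.15 |
| 40% | 0.385 | 0.83 to 1.21 |
| 61% | 0.562 | 0.76 to 1.31 |

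The 20% to 30% rows are meant for AUC and the 61% row for a high Cmax variability. At 15/10 the limits hardly change (0.885 to 1.13 at 25%).

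**2. Ambiguity of the ratio.** If individual ratios were averaged arithmetically, the result would exceed the geometric mean ratio by the factor exp(sw²) = 1 + CVw². That is 1.04, 1.06 and 1.09 at CVw 20%, 25% and 30%.

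**3. Period effect, shift of an unadjusted ratio.** Factor = 1.2^((n1 − n2)/N).

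- 13/12: 1.2^(1/25) = 1.007, a shift of 0.7%.
- 15/10: 1.2^(5/25) = 1.037, a shift of 3.7%.

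**4. Period effect, loss of precision.** The within-patient log ratio has variance 2sw², which is 2 × 0.0606 = 0.121 at CVw 25%. A period effect left in adds about (ln 1.2)² = 0.0332. The increase is 0.0332/0.121 = 27% in variance, or √1.27 = 1.13, about 13% in standard deviation.

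**5. Carryover.** The 14-day washout is 336 h. At a 40 h half-life that is 336/40 = 8.4 half-lives, leaving about 0.3%. At 56.4 h, the longest in the table, it is 6.0 half-lives, leaving 1.6%. Carryover is not part of this point.

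**The case against.** **The trial is exploratory.** Section 6.1 calls it "Pilot clinical trial Phase I, single-center, open-label, single dose", the verb in section 5.1 is to explore, and the main objective in the Summary does not mention iv at all. Section 7.1 justifies 25 patients for description. This stands: no hypothesis test or power calculation is owed, and a descriptive aim is legitimate. It does not remove the mismatch, because section 5.1 makes the primary objective a comparison and an estimate of bioavailability still needs its precision.

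**Model detail belongs in an analysis plan.** This stands in part. Log scale, model terms and interval level are often left there. But section 12.1 is not merely brief: it states a one-route description for the primary parameters and places the paired methods elsewhere.

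**An sc/iv comparison of Cmax and tmax is of limited value.** Iv is a 30-second injection, so iv tmax is expected at or near the first sample, and iv Cmax depends on sampling time. This limits interpretation, but it is no reason to leave the iv values undescribed.

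**Stronger readings the text does not support.** A reader might infer that the ratio is a raw-scale mean and so biased upward; section 12.1 gives no scale, and a ratio of geometric means would satisfy it. A reader might infer that period and sequence are excluded; the protocol is silent on them. A reader might infer that 25 patients cannot be balanced; the Summary sets a minimum of 25 evaluable patients, so 13/13 is allowed, and the randomisation list in Annex IX is not shown.

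**Conclusion.** The point holds as a mismatch between objective and planned analysis, of moderate weight. The primary parameters are to be described for sc only, the AUC0-t ratio has no stated scale, averaging rule or interval, and Cmax and tmax have no planned sc/iv comparison.

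A large bias is not shown. Even with an assumed 20% period effect the shift is 0.7% at 13/12 and 3.7% at 15/10. The 4% to 9% excess arises only if individual ratios are averaged arithmetically, at CVw 20% to 30%. The larger effect is on precision: about 27% more variance in the log ratio at CVw 25% if such a period effect stays in the residual. The main loss is the interval itself, about ×/÷1.10 to 1.15 for AUC at CVw 20% to 30%.

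That AUC range should not be carried over to Cmax, where CVw 61% gives 0.76 to 1.31. It may also be optimistic for AUC: the third column of the section 4.1.2 table has AUC standard deviations of 49% (4,220/8,570) and 58% (20,900/35,800) of the mean, although these too are between-subject. All sizes rest on the assumed CVs and the assumed period effect.

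**What to change.** Reword section 12.1 as follows:

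- Describe the pharmacokinetic parameters for both routes.
- Analyse log AUC and log Cmax with sequence, period, route and patient within sequence.
- Report the sc/iv geometric mean ratio with a 90% confidence interval, stated to be an estimate and not a powered test.
- Take AUC over the same time span for both routes within each patient. The 24-hour sample is conditional on the length of stay (sections 9.1.2 and 9.2.1), so the last time point could otherwise differ between a patient's two periods.
- Summarise tmax by the median within-patient difference.

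The cost is wording in the analysis section. No extra patients, samples or visits are needed, since the parameters are already derived for each patient after each route.

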**13. - Primary endpoint.**

Be assessed palonosetron pharmacokinetic parameters following:

Cmax = maximum concentration.

AUC _0-t_ =               area under the plasma concentration-time curve to the last extraction (time t).

tmax = time to reach Cmax.

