**9.** **ASSAY DEVELOPMENT**

***9.1.*** ***Study Plan***

*9.1.1.*        *Selection stage*

In the 20 days before the start of the intervention phase of the study will be the selection of volunteers. This phase will recruit 25 patients will be informed of the design, objectives and possible risks of the study. Each patient will have the opportunity to ask any questions you want to research. Before any test is obtained written informed consent.

They perform a complete medical history that includes:

• Detailed anamnesis.

• Complete physical examination with assessment of functional status (ECOG scale).

• Registration of drugs administered to the patient at the time of inclusion.

• Laboratory tests:

Hematology: CBC.

Biochemistry: blood: cre atinina, urea, SGOT (AST), SGPT (ALT), GGT, total bilirubin, electrolytes

In case the patient has already been subjected to this analysis in the 10 days prior to administration of the medication can not be repeated.

With all these data verify the eligibility of patients to participate in the study.

*9.1.2.*        *Intervention phase*

The intervention phase will consist of two periods in which the patient will receive the study medication. Each will have a minimum duration of 12 hours, separated by at least two weeks washout period. In each volunteer will receive a dose of palonosetron 250 μ g intravenously or subcutaneously, according to the randomization code. Before the second administration of the drug is verify that the patient has adequate hepatic and renal function.

Will place a peripheral venous independent pathway by the patient receive chemotherapy and palonosetron, through which the blood samples drawn for determination of the drug.

They undertake every single day of intervention:

- Determination of the SBP and DBP, FC and temperature in a sitting position before administration of the study medication.

Blood drawn at baseline (5 ml).

Assessment of pain by visual analog scale.

After drug administration was performed:

Blood samples (5 ml) at the following times: end of infusion, 10 - 15 - 30 - 45 - 60 mins, 1,5 - 2 - 3 - 4 -8 to 12 hours. If income permits 24 hours.

Collection of urine during the 12 hours of study.

Subjective assessment of pain using a visual analog scale at the time: 1 to 4 and 8 hours.

Physical examination of the administration at 1, 4 and 8 hours after administration.

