***9.2.*** ***Handling of blood samples***

*9.2.1.*        *Extractions*

After administration of palonosetron, there will be blood samples (5 ml) at the following times: end of infusion, 10 - 15 - 30 - 45 - 60 mins, 1,5 - 2 - 3 - 4 -8 to 12 hours. If income permits 24 hours.

Blood will be drawn from the vein. EDTA tubes are used (5 ml).

Samples were centrifuged at 3500 rpm for 10 minutes at 4 ° C within 30 minutes after removal. The resulting plasma was separated into two aliquots for determination of palonosetron, and freeze at -70 ° C until shipment to the laboratory for analysis. Palonosetron determining aliquots of plasma will be by high resolution liquid chromatography with mass spectrometer detection (LC / MS). The conditions of sample handling can be modified depending on the analysis technique, which is in development.

*9.2.2.*        *Labelling*

Samples for the determination of palonosetron is labeled with the following information:

-           Line 1:               Name of the active ingredient (palonosetron).

-           Line 2:               study identification code. Route of administration. Aliquot (original or duplicate).

-           Line 3:               Number of subject randomization. Initials. Period administration.

-           Line 4:               The time of extraction.

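### The sc/iv bioavailability ratio uses AUC0-t with no common t: one patient's areas can cover 12 h by one route and 24 h by the other

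*Protocol*

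**What the plan says.** Section 12.1 lists AUC0-t among the parameters that "will be determined for each subject following administration of each treatment". It defines it as the "area under the curve versus time to the last quantifiable sample (time t), calculated using the trapezoidal method". Section 10.1 does the same: "from time 0 to the last quantifiable concentration (time t) calculated by the trapezoidal method". Bioavailability is then the ratio of the sc to the iv value ("Bioavailability is calculated in this way by calculating the ratio of AUC", section 12.1).

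Section 9.2.1 sets the draws after the end of infusion at "10 - 15 - 30 - 45 - 60 mins, 1,5 - 2 - 3 - 4 -8 to 12 hours" and adds: "If income permits 24 hours". Section 9.1.2 repeats this. In context the translated word "income" means the hospital admission. On the length of the two periods, section 9.1.2 says: "Each will have a minimum duration of 12 hours". No upper limit is given.

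No section requires the 24-h draw in both periods or in neither, cuts the two areas at a common time, or bases the ratio on an area extrapolated to infinity.

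**The concern.** A ratio of two truncated areas compares routes only if both are truncated at the same time. Here t is set separately by subject and treatment, and the last possible draw depends on an admission. Palonosetron is eliminated slowly: at a half-life of 40 h the concentration falls only about 19% between 12 h and 24 h (1 − 2^(−12/40) = 0.19). The second 12 hours therefore add a large area to whichever period has the late draw.

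In such a patient the ratio partly measures length of stay. AUC0-t is a primary parameter, this ratio is the only bioavailability estimator in the protocol, and section 7.1 justifies 25 patients partly by the wish to describe bioavailability.

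**Working it through.** The protocol gives no figure for this effect, so there is none to reproduce.

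**Inputs (section 4.1.2 and its table).** Half-life is about 40 h in the text, and 37, 42.8 and 56.4 h in the table. At 0.25 mg iv, AUC0-24 is 8,900 ng·h/l (multiple-day dosing study in healthy subjects) and AUC0-∞ is 20,700 ng·h/l (infusion-time study in healthy subjects). Total clearance is 173 ml/min.

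**iv AUC0-24/AUC0-12, one-phase decline.** The ratio is 1 + 2^(−12/t½):
- 37 h: 1.80
- 40 h: 1.81
- 42.8 h: 1.82
- 56.4 h: 1.86

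**Same ratio, two-phase decline.** The area beyond 24 h is 20,700 − 8,900 = 11,800. If the terminal phase already holds from 12 h, AUC12-24 = 11,800 × (2^(12/t½) − 1).
- 40 h: 11,800 × 0.2311 = 2,728; AUC0-12 = 8,900 − 2,728 = 6,172; ratio 8,900/6,172 = 1.44
- 37 h: 1.50
- 42.8 h: 1.40

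These figures combine two studies and are approximate. With dose over clearance as AUC0-∞ (250,000/(0.173 × 60) = 24,085) and 40 h, the ratio is 1.65, between the two sets.

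**Error in a discordant patient.** The factor is about 1.4 to 1.9. If the true ratio is 1 and absorption is fast, the result is about 1.4 to 1.9 when sc has the longer t. When iv has it, the result is about 1/1.86 = 0.54 to 1/1.44 = 0.69.

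**Effect on the group.** Let p be the proportion of discordant patients and r the factor. With an assumed within-patient CV of 25%, the variance of the log ratio is 2 × ln(1 + 0.25²) = 0.121. Discordance in random direction adds p(ln r)². If every discordant patient has the longer t under sc, the geometric mean ratio is multiplied by r^p. (ln 1.44)² = 0.133 and (ln 1.86)² = 0.385.

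| p (assumed) | Added variance | Increase in variance | One-directional shift (upward) |
|---|---|---|---|
| 10% | 0.013 to 0.039 | 11% to 32% | 4% to 6% |
| 40% | 0.053 to 0.154 | 44% to 127% | 16% to 28% |

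**What a common window leaves.** Assumptions: linear trapezoid on the protocol's sampling times, true bioavailability 1, half-life 40 h, first-order sc absorption (the documents hold no sc data).

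| Absorption rate ka | sc/iv ratio to 12 h | sc/iv ratio to 24 h |
|---|---|---|
| 1 to 5 per hour | 0.92 to 0.99 | 0.96 to 1.00 |
| 0.25 per hour | 0.69 to 0.81 | 0.84 to 0.91 |

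A common t removes the mismatch. A smaller truncation bias remains if absorption is slow.

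**The case against.** **The periods are meant to match.** Section 6.3 says they differ only in route, section 4.2 plans a 12-h stay, and consecutive cycles may well have similar admissions. This bears on how often discordance occurs, and it may be rare. It does not prevent it: a general design statement does not govern a draw that the same protocol makes conditional on the admission.

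**The study is an exploratory pilot.** The PK analysis is descriptive and the ratio has no acceptance limit. Section 12.1 does not say whether the ratio is taken per patient or from group means. All of this stands and limits the consequence. Cmax and tmax are unaffected unless the maximum falls at 24 h.

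**An analysis plan could set a common t.** It could, but section 12.1 already names the estimator and its t, so such a plan would depart from the protocol.

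Three stronger readings are tempting and not supported:
- *A factor of 2 or more.* The table's 3 µg/kg column (8,570; 35,800; 56.4 h) gives 27,230 × (2^(12/56.4) − 1) = 4,327 for 12-24 h and 4,243 for 0-12 h, a ratio of 2.02. A declining iv curve cannot have more area in its second 12 h than in its first, so this is not a usable bound. Values of 2 or more arise only for the sc curve, with assumed slow absorption and no early distribution phase.
- *A biased overall comparison.* Nothing suggests that stay depends on route. Discordance in both directions would partly cancel in the mean and show up as extra spread.
- *Two contradictory definitions of AUC0-t.* Summary item 13 ends the area at the last draw, sections 10.1 and 12.1 at the last quantifiable one. Section 3.1 joins the two, and they differ only if the last sample is below quantification. This is a wording matter.

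**Conclusion.** The concern holds. As written, the bioavailability ratio can compare areas over 12 h and 24 h within one patient. In such a patient it is wrong by a factor of roughly 1.4 to 1.9, in the direction of the route with the longer t. The lower end rests on a two-phase decline built from two studies, the upper end on a one-phase decline with half-lives of 37 to 56.4 h.

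The effect on the trial result depends on the number of discordant patients, which the documents do not let one estimate. The 10% and 40% scenarios and the 25% CV are illustrations. The finding is that a stated rule permits an avoidable error in a primary comparison; it does not show that the overall estimate will be biased.

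**What to change.** In section 12.1, compute the sc/iv AUC ratio over the same time window in both periods of each patient. Make AUC0-12, for all patients, the main ratio and report it as 0-12 h relative exposure. Report the AUC0-24 ratio alongside for patients with a 24-h sample in both periods. Use one AUC wording in Summary item 13 and sections 10.1 and 12.1.

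No new samples are needed, but there are two costs. Unpaired 24-h samples leave the ratio. A 12-h window also understates sc bioavailability if absorption is slow, by the amounts shown for ka 0.25 per hour. That is why the 12-h result needs its label and the paired 24-h ratio should stand next to it.
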